### Study setting

A total of 16 sites (maternity units) agreed to take part in the OptiBIRTH trial initially: five from Ireland, five from Italy and six from Germany. In order to be eligible for participation, each site had to have a VBAC rate of less than 35 % and to provide a letter from the lead obstetrician (and, when available, the lead midwife) stating that they were willing for their institution to join the study. However, one of the German sites was withdrawn from the trial because of failure to recruit any participants in the first 6 months.

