## Methods/Design

### Design

This is a cluster randomised trial of maternity units in three countries with relatively low VBAC rates (Germany, Ireland and Italy). The units represent a variety of healthcare settings (small, medium and large units, with annual births of 2,000 to 8,500) in both urban and rural locations [14]. For the purposes of the randomisation, two maternity units in the same city in Germany were considered as a single cluster for the purposes of the trial.

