### Randomisation

The unit of randomisation in the trial is the maternity unit (the ‘site’). Randomisation had to be done in advance of recruiting women to participate in the trial to allow appropriate preparations to be made in each site. Further, given the temporal nature of pregnancy, it is not possible to hold randomisation until all women in each participating site have been recruited, because some women would have given birth by the time the last woman would have been recruited. However, as with cluster trials in which the participants cannot be blinded to the intervention, once the sites had been randomised, it is possible that recruitment of women to the trial was influenced by the knowledge of whether or not they would receive the OptiBIRTH intervention at that site. Hence, the primary analyses for the trial (see below) will consider data at the level of each site as a whole, rather than at the level of the women who were approached and formally recruited.

Within each of the three countries, the maternity units were matched by their annual number of births and then by VBAC rate. They were matched in either pairs or triplets and then randomised 1:1 or 2:1 to intervention or control, respectively. The randomisation was done using the random number generator in Microsoft Excel [RAND], with the first site in each matched pair or triplet being assigned a random number between 0 and 1. If the number was below 0.500, the site was allocated ‘OptiBIRTH intervention’. If it was above 0.500, the site was allocated ‘control’. If the number had been exactly 0.500 the randomisation would have been done again, but this did not happen. Where a matched pair had been formed, the second site was automatically allocated the opposite of the first site. Where a matched triplet had been formed, if the first site was allocated to the control group, the other two sites were automatically allocated to the intervention group. If the first site was allocated to the intervention group, the randomisation was repeated for the second site, and the third site was automatically allocated to the opposite of the allocation for the second site.

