### Sample size assumptions and estimates

The sample size for this cluster randomised trial was derived by adjusting an estimate for the sample size for an individually randomised trial to allow for clustering. This was done by inflating the estimate by the design effect given by 1 + (ñ-1)ρ, where ñ is the average cluster size and ρ is the estimated intra-class correlation coefficient (ICC) for this study. With a background proportion of successful VBAC of 25 % and an ICC of 0.05, 12 trial units would be required, each containing 120 participating women (840 women in the intervention group and 840 women in the control group), to detect a 15 percentage point difference in successful VBACs (that is, an increase from 25 % in the control group to 40 % in the intervention group), with power of at least 80 % and an alpha level of 0.05. If the true ICC values are less than 0.05, the power of the study will increase. To allow for a loss to follow-up of 20 % of women and the possibility that one site per country will drop out of the trial, 15 trial units (16 maternity sites) were randomised across three countries.

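### The planned equal arms of 840 match neither the 9:6 allocation that the randomisation produces nor 12 units of 120 women, and no 12-unit outcome reaches the stated 80 % power

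*Protocol article*

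**What the plan says.** All references are to the protocol article.

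- **Sample size assumptions and estimates.** The requirement is that "12 trial units would be required, each containing 120 participating women". The same sentence gives this as "840 women in the intervention group and 840 women in the control group". The target is "an increase from 25 % in the control group to 40 % in the intervention group", at an ICC of 0.05, "with power of at least 80 % and an alpha level of 0.05". The section does not say whether the test is one- or two-sided. Fifteen units were randomised to cover a 20 % loss of women and "the possibility that one site per country will drop out of the trial".
- **Study setting.** The 16 sites are "five from Ireland, five from Italy and six from Germany". One German site was later withdrawn; its arm is not given.
- **Design.** For the randomisation, "two maternity units in the same city in Germany were considered as a single cluster".
- **Randomisation.** Matching was done within each country: "They were matched in either pairs or triplets and then randomised 1:1 or 2:1 to intervention or control, respectively".

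**The concern.** The sample size section assumes two arms of equal size and does not mention unequal allocation, while the randomisation section describes a scheme that favours the intervention arm. If the scheme fixes the split, the stated arm sizes are not those of this design.

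The arm sizes also fail to match the number of units in their own sentence. A reader cannot tell which of the three figures (12 units, 120 women per unit, 840 per arm) the power claim rests on.

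At stake is the promise of at least 80 % power. The allowance for lost sites is expressed as a count of units, without regard to arm. Under a 9:6 start, losing control units costs more than losing intervention units, and the section does not show this.

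**Working it through.** **1. Allocation.** Ireland has 5 units and Italy 5. Germany has 6 sites with two merged, so 5 units. The total is 15, as the sample size section says. Five units divide into pairs and triplets in only one way: 2 + 3. A pair gives 1 intervention and 1 control. Every branch of the triplet rule ends with 2 intervention and 1 control. Each country therefore has 3 intervention and 2 control units, and the trial has 9:6. At 120 women per unit this is 1,080 and 720.

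**2. The sentence's own total.** 12 × 120 = 1,440, or 720 per arm. The stated 840 + 840 = 1,680 needs 1,680 / 120 = 14 units, or 12 units of 1,680 / 12 = 140 women.

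**3. Reproducing the stated size.** Design effect = 1 + (120 − 1) × 0.05 = 6.95. The sample size per arm for two proportions (normal approximation, pooled variance under the null) at 80 % power is:

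- Two-sided 0.05: 152 × 6.95 = 1,057 per arm (1,056.4, rounded up); 1,057 / 120 = 8.8, so 9 units per arm.
- One-sided 0.05: 120 × 6.95 = 834 per arm; 834 / 120 = 6.95, so 7 units and 840 women per arm.

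So 840 per arm is recovered only as a one-sided test with 7 + 7 = 14 units. No variant tried at 80 % power or more with units of 120 gives 12 units.

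**4. Units left after losing one per country.** Each country goes from 3:2 to 2:2 (intervention unit lost) or 3:1 (control unit lost). Over three countries the 12 remaining units are 6:6, 7:5, 8:4 or 9:3. If the lost unit is random within country (an assumption), the probabilities are 21.6 % (that is, (3/5)³), 43.2 %, 28.8 % and 6.4 %.

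**5. Power.** The effective size of an arm is units × 120 / 6.95. Power = Φ[(0.15 − z × s₀) / s₁], where s₀ is the pooled and s₁ the unpooled standard error. For 9:6 the effective sizes are 155.4 and 103.6, s₀ = 0.0601 and s₁ = 0.0579. Two-sided: Φ[(0.15 − 1.96 × 0.0601) / 0.0579] = 71.1 %.

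| Intervention:control units | Two-sided | One-sided |
|---|---|---|
| 7:7 (840 per arm) | 70.4 % | 80.4 % |
| 9:6 | 71.1 % | 81.2 % |
| 6:6 | 63.7 % | 74.8 % |
| 7:5 | 61.8 % | 73.5 % |
| 8:4 | 57.3 % | 69.7 % |
| 9:3 | 49.4 % | 62.6 % |

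A notional equal split of 15 units (7.5:7.5) gives 73.4 % two-sided, so the unequal allocation alone costs 73.4 − 71.1 = 2.3 points.

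**6. With 20 % of women lost.** It is not stated whether 120 is before or after this loss. If before, 96 women per unit remain and the design effect is 1 + 95 × 0.05 = 5.75. Power is then 69.6 % two-sided (80.0 % one-sided) at 9:6. For 6:6, 7:5, 8:4 and 9:3 it is 62.2 %, 60.3 %, 55.8 % and 48.0 % two-sided (73.6 %, 72.2 %, 68.4 % and 61.3 % one-sided).

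**The case against.** Several points on the other side stand.

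- **The 12-unit count is consistent.** Fifteen minus one per country is 12, and 6:6 is possible. A reader might infer that the 12-unit fallback contradicts the randomisation. It does not; only equality of the arms is not assured.
- **The allocation is not the main cause of low power.** A reader might blame the 9:6 split for the fall to 49 %. But 12 units in equal arms already give only 63.7 % two-sided, and 7:5, the likeliest split under random loss, costs a further 1.9 points. The 9:3 case is rare under the same assumption.
- **Required size and yield are different quantities.** The 840 per arm is a requirement; 1,080 and 720 are what all 15 units would yield before losses. The second should not simply replace the first.
- **Sidedness matters.** On a one-sided reading, 9:6 meets 80 % before any unit is lost. That does not rescue the 12-unit case, where the best one-sided figure is 74.8 %.
- **The primary analysis is different.** It compares site-level changes in VBAC rate using routine data on all women with one previous caesarean. A reader might conclude that this analysis has 49 % to 71 % power. The documents do not support that, because the calculation is for recruited women and does not model a before-after change.
- **The allocation is done.** Randomisation took place in April 2013, so the correction changes what is reported and not how the trial runs.

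**Conclusion.** The point holds as an error in the sample size section. The 9:6 split follows with certainty from the site counts, the merged German cluster and the matching rule, so equal arms are not what this design produces. The figure of 840 per arm also contradicts 12 units of 120 under any allocation. No 12-unit outcome reaches the stated 80 %: power is 49 % to 64 % two-sided and 63 % to 75 % one-sided. Most of that gap comes from having too few units; unequal allocation adds about 2 points at 15 units, and up to 14 points (63.7 % to 49.4 %) if all three lost units are control units.

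The figures assume equal unit sizes, the article's ICC and rates, and a normal approximation. A t-approximation for few clusters lowers two-sided power to about 67 % at 9:6 and 56 % at 6:6. The effect of the German withdrawal cannot be settled from the article, which gives neither the site's arm nor whether it belonged to the merged cluster.

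**What to change.** Restate the sample size section so that the number of units, women per unit, women per arm and sidedness of the test agree with one another. State that the matching gives 9 intervention and 6 control units. Give the power at 9:6 and after loss of intervention or of control units, with the 20 % loss of women included, and use these figures in place of the claim of at least 80 % wherever it is not met. Keep the required size separate from the expected yield of the 15 units.

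Label the figures as applying to the comparison of recruited women, not to the site-level before-after primary analysis. Showing unit loss for both arms avoids disclosing the arm of the withdrawn German site, which need not be revealed while site information is being withheld.

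The cost is some rewording and one recalculation, and a less favourable power statement. Allocation and recruitment are unaffected.

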### Recruitment and consent

In order to maintain the integrity of the cluster randomisation, each woman in each site will be screened for eligibility for OptiBIRTH, using a pre-designed Trial Screening and Register Form. Although all those who are eligible could be considered to have been randomised, it will only be possible to use data for those who give their consent.

Following screening, women who are judged eligible for OptiBIRTH will be informed of the study verbally and will receive a ‘study information pack’, including a detailed information leaflet and a consent form. This will be done by the midwives who are providing their antenatal care and takes place at the earliest opportunity in the woman’s interaction with the maternity unit. If a woman presents too late in her pregnancy to avail herself of the antenatal classes or the online resources, she will not be approached about OptiBIRTH. Women, having had time to consider the study information and agreeing to participate in the trial, will sign and return the consent form to the local research office. On receipt of the signed consent form, women will be contacted by the local postdoctoral researcher (or designated hospital midwife) and provided with further details on accessing the trial processes (intervention sites only).

When seeking their consent, women will be offered the opportunity to participate in the trial at one of two levels, which relate to both their use of the various elements in the intervention and the provision of data. If the OptiBIRTH intervention succeeds in building a community of practice at the site which is more favourable to VBAC, this should impact all women at the site, not just those who choose the ‘full participation’ option and attend the antenatal classes or access the online resources.

The two levels of participation are as follows:Full participation: women in the intervention sites would choose this option if they wanted to be able to attend the OptiBIRTH antenatal classes and access the online resources. In both the intervention and the control sites, women who choose this option are agreeing to complete the health surveys and a diary of healthcare expenses and to allow the OptiBIRTH researcher to access their healthcare records and those of their babies.Routine data only: women choose this option if they are willing to give permission for the OptiBIRTH researcher to access the healthcare records for themselves and their baby, but do not wish to attend the antenatal classes or access the online resources (in the intervention sites) or to complete the health surveys and diary of healthcare expenses (in both intervention and control sites).

### Data collection

Pre-designed data extraction forms will be used to collect all study outcome data. These include forms for participant self-report of antenatal and postnatal health and wellbeing and healthcare resource use, as well as expenditure surveys and clinician-report labour and birth outcome data collection forms. Where relevant, the forms will be provided to the participants and they will be asked to complete and return them to their hospital. Other data (such as routine data on birth events) will be collected at each participating site by each country’s national postdoctoral researcher or a designated research assistant. Each national coordinating team will use specially created Microsoft Access forms to enter and store their data before submission of the data in encrypted form to the OptiBIRTH trial and data management centre. The relevant data are to be submitted for each woman at each stage in the OptiBIRTH trial (from screening through to the data gathered on the postnatal follow-up forms). Each country’s national coordinating/postdoctoral researcher will audit approximately 5 % of the records for each participating site during their visits to those sites.

### Data management and validation

Data will be submitted by encrypted email to OptiBIRTH’s trial and data management centre (Centre for Public Health, Queen’s University Belfast) monthly and stored in the trial database (Microsoft Access 2007). Appropriate validation rules are in place for each field in the OptiBIRTH data. Cross-validation routines have been established, where the content of one field would determine the validity of data in another field. For example, if a woman has a spontaneous vaginal birth, the fields for capturing data following a caesarean section should not be completed. The OptiBIRTH trial database will contain identifiable information and, as such, conforms to legal requirements as defined in the UK Data Protection Act 1998. In response to this Act, Queen’s University Belfast issued a Policy Statement and developed robust data protection recommendations that the Centre for Public Health at Queen’s University Belfast adhere to. Given that the database contains identifiable data, the potential risk associated with this database relates to a potential breach of participant confidentiality, whereby a party not involved directly in the study gains access to identifiable data, and the aforementioned policies and practices are designed to prevent this.

### Data analysis

Statistical analysis plans will be prepared for the analyses of both the clinical and the cost-effectiveness data, and made available separately to this protocol. Where possible, the main analysis will be by ‘intention-to treat’ but this is not always possible in a cluster randomised trial where, by the nature of the intervention, the recruiters and the potential participants are aware of their allocated intervention before they are asked to provide their consent. Therefore, the principal analysis to test the effect of the intervention at the site level will compare differences in the primary outcome, namely the proportions of VBAC, between the intervention and control sites. The comparison of VBAC rates in each of the participating sites will compare the change in the VBAC rates in the intervention sites versus the change in the control sites between the calendar year 2012 (that is, before the OptiBIRTH intervention was available to any hospital) and, if possible, the 12-month period after the month that the last OptiBIRTH baby is born in each hospital. However, for some hospitals, it might be necessary to use the data for the calendar year (that is, January to December) that follow the birth of the last OptiBIRTH baby in that hospital because of the practical difficulties of accessing hospital level data for periods other than calendar years.

In addition to the primary analyses at the level of the hospital, we will analyse the data for the women who agree to take part in the trial and their babies, in order to assess the effects of the intervention on the secondary outcomes listed above. Where outcomes have been collected as continuous variables (for example, duration of labour) they will be analysed as continuous data to compare the intervention and control sites. Likewise, dichotomous data (for example, breast feeding at 3 months) will be used to compare the proportions in the intervention and control sites. The analyses will adjust for whether the woman had had any prior vaginal birth or prior VBAC, and her BMI and age. We will conduct subgroup analyses for these adjustment variables and the three countries. Our hypothesis is that the effects of the intervention will not be so heterogeneous across these subgroups to invalidate the calculation of an overall result for the trial as a whole.

### Trial oversight

#### Trial management group

There will be monthly Skype or teleconferences of the Trial Management Group, comprising the principal investigators and postdoctoral researchers from each country, in addition to the principal investigator and data manager for the trial, the project coordinator for the OptiBIRTH project as a whole, and other members of the OptiBIRTH project as appropriate to the specific meeting.

#### Trial steering committee

The Trial Steering Committee (TSC) comprises the members of the overall Steering Committee for the OptiBIRTH project as a whole. This group meets quarterly, usually by Skype or teleconference but with one face-to-face meeting per year. Summary reports for each site, each country and the trial as a whole will be prepared every 3 months for the OptiBIRTH TSC, showing the data for each 3-month period and for the full duration of the trial to date. These reports contain data relating to the management of the trial to show its progress without revealing interim results.

#### Data monitoring committee

To optimise participant safety and the scientific integrity and credibility of the results of the trial, an international Data Monitoring Committee (DMC) will conduct an interim analysis of data from approximately 400 to 700 women who have birthed and will provide an interim report. They will be provided with unblinded data on the VBAC rate at each site in the year before the OptiBIRTH trial began, the number of women recruited in each site and the proportion of those who are known to have birthed who did so by spontaneous vaginal delivery or with the use of ventouse or forceps. This initial assessment of the effects of the intervention on VBAC and safety will influence the decision on whether control sites should be offered the intervention on completion of the trial within the available funding timeframe. The DMC will assess participant safety and whether either intervention is showing a much stronger or weaker effect than expected. It will make recommendations concerning the future of the study to the TSC.

### Ethical considerations

The ethical issues involved in this study are the key principles of ensuring the protection of human rights, the maintenance of scientific integrity, the minimising of harm and maximising of benefit and ensuring justice and equity, autonomy and informed consent, confidentiality, data protection and privacy. Ethical approval was granted by the Faculty of Health Sciences, Trinity College Dublin, Ireland and regional Research Ethics Committees for all participating study sites in each participating country. A list of the relevant committees was provided to the journal as part of the approval process for this manuscript, but, as noted above, identifying information for the sites is not included in this published protocol to reduce the possibility that this knowledge might influence referral of pregnant women to the participating sites during the recruitment or follow-up phases for the trial.

### Ancillary studies

Should the opportunity arise to conduct a SWAT (Study within a Trial) in OptiBIRTH, this will be discussed with the TSC and implemented with their approval. The SWAT programme has been developed by the Northern Ireland Network for Trials Methodology Research as a means to encourage the conduct of research within research, to reduce uncertainties about the most appropriate and effective methods to use in randomised trials and other evaluations of health and social care [34, 35].

### Dissemination

The main findings of OptiBIRTH will be published under an Open Access model and will be presented at relevant national and international conferences. The current intention is that the analyses for the participating women will be published following collection of the final outcome data for all of those women.

## Discussion

Recruitment to the OptiBIRTH trial is expected to close in all sites in 2015, with all participating women expected to birth by the end of the year. Recruitment has been slower than anticipated, in part because birth rates have fallen at several of the sites. As with cluster randomised trials in general, it has not been possible to recruit all potentially eligible women at each site. Among the reasons for this are that some of the women who were offered participation in the trial did not wish to join and because of challenges in fully initiating the study in each site. This may introduce differences between the participants in the intervention and control sites, which reinforces the importance of the primary analyses being a comparison of the VBAC rates for all women with one previous caesarean section at each site before and after the study period using routine data from each site. If the OptiBIRTH intervention succeeds in increasing VBAC rates, its application across Europe might avoid 160,000 unnecessary caesarean sections every year, which occur at an extra direct annual cost of more than €150 million.

